## Abstract

**Introduction:**

The presence of increased oxidative stress and airway inflammation has been proven in subjects with chronic obstructive pulmonary disease (COPD). Several studies have demonstrated that drugs with antioxidant and anti-inflammatory properties such as *N*-acetylcysteine (NAC) can reduce the rate of exacerbations in patients with COPD. However, the beneficial effects of NAC in early-stage COPD are minimally discussed. We are investigating whether high-dose NAC has therapeutic effects in Chinese patients with early-stage COPD.

**Method and analysis:**

A randomized, double-blinded, placebo-controlled, parallel-group, multicenter clinical trial is evaluating the efficacy and safety of NAC for the long-term treatment of patients with early-stage COPD at 24 centers in China. Subjects aged 40–80 years and recruited by physicians or researchers with special training will be randomized to either NAC 600 mg twice daily group or matching placebo group for 2 years. Measurements will include forced expiratory volume in 1 s (FEV_1_), the number of COPD exacerbations, health-related quality, and pharmacoeconomic analysis.

**Discussion:**

Currently, there are no randomized controlled trials with high-dose *N*-acetylcysteine (600 mg twice daily) for patients with mild-to-moderate COPD (GOLD I–II). We designed this multicenter randomized controlled trial (RCT) to assess the effectiveness, safety, and cost-effectiveness of long-term treatment with high-dose *N*-acetylcysteine. The results of this trial may guide clinical practice and change the standard of early COPD management.

**Trial registration:**

Chinese Clinical Trial Registry ChiCTR-IIR-17012604. Registered on 07 September 2017.

## Introduction

Chronic obstructive pulmonary disease (COPD) is a common, preventable, and treatable disease that is characterized by persistent respiratory symptoms and airflow limitation that is due to airway and/or alveolar abnormalities usually caused by significant exposure to noxious particles or gases [1]. COPD led to 3.2 million deaths in 2017 and become the third leading cause of death in the world in 2030 [2]. Acute exacerbation of COPD leads to a rapid decline of lung function, damage of health status, a decrease of exercise endurance, a high hospitalization rate, and an increase of social burden [3]. More than 70% of patients with COPD were at stage I or II which Global Initiative for Chronic Obstructive Lung Disease (GOLD) defined as early-stage COPD [1]. Their respiratory symptoms are usually mild or asymptomatic and rarely seek medical attention before the disease worsens [4, 5]. Recent studies have found that the annual decrease rate of forced expiratory volume in 1 second (FEV_1_) in patients with early COPD is higher than that in patients with severe COPD (GOLD stages III–IV) [6, 7]. Effective prevention and treatment have been explored for earlier stages of COPD. Our previous result also proved that early treatment of COPD with tiotropium or NAC resulted in a significant health benefit, delaying the annual decline of FEV_1_ or reducing COPD exacerbation rate [8, 9]. Recently, scholars have shown increasing interest in the potential mechanism and economic burden of COPD. Therefore, it is necessary to further study its pathogenesis and seek alternative treatment modalities.

Several factors such as chronic inflammation, mucus hypersecretion, and airway oxidative stress play an important role in the occurrence and development of COPD, leading to the loss of adhesion between alveoli and small airway and the decrease of lung elasticity [1]. Therefore, drugs with antioxidant, anti-inflammatory, and mucolytic characteristics may be helpful in the treatment of early-stage COPD.

*N*-Acetylcysteine (NAC) is a mucus soluble derivative of amino acid l-cysteine, which can reduce the viscosity of airway secretions and increase the ciliary clearance rate, but it has a more potent effect in antioxidant and inflammatory regulation [10, 11]. In vivo and in vitro studies extensively proved that NAC has both direct/indirect antioxidant and anti-inflammatory properties [12–14]. Furthermore, the convenience of oral administration together with its low price may be suitable in the long-term treatment of COPD patients in less-developed areas. The long-term efficacy and safety of NAC have also been demonstrated in some lung diseases such as idiopathic pulmonary fibrosis and cystic fibrosis [15, 16]. Several studies have shown that treatment with NAC (400–1200 mg per day) reduced rates of acute COPD exacerbations [17, 18], improved pulmonary function [19, 20], and prevent hospital readmissions [21, 22]. We also noted in our previous studies that the drug can significantly reduce the acute exacerbation rate of patients with moderate COPD patients (GOLD II), but has little effect in reducing the acute exacerbation of patients with severe COPD (GOLD III), suggesting that *N*-acetylcysteine may play a more important role in the early-stage of COPD [9].

However, (1) with these inconsistencies of the results above, the effect of NAC in COPD is still indetermination; (2) the majority of these studies recruited moderate-to-severe COPD patients and had a relatively short follow-up period, a design only including early-stage COPD with long-term follow-up period should be carried through; (3) the pharmacological effect of *N*-acetylcysteine was dose-dependent, some 400–800 mg/day trials did not achieve significant effects in reducing the acute exacerbation rate and annual FEV_1_ decline rate. Thus, we designed a 2-year trial titled, “High-dose N-acetylcysteine for long-term, regular treatment of early-stage chronic obstructive pulmonary disease (GOLD I-II) in China” to investigate the efficacy and safety of 1200 mg/daily *N*-acetylcysteine in lung function, quality of life, and number and duration of acute exacerbations of COPD patients.

## Methods and analysis

### Study design

This is a 2-year, randomized, double-blinded, placebo-controlled, parallel-group, multicenter trial of longitudinal treatment with high-dose NAC (600 mg twice daily) for patients with early-stage COPD. After a 1-week run-in period, 1000 patients with mild-to-moderate COPD will be randomly assigned in a 1:1 ratio to treatment with either NAC 600 mg twice daily or matching placebo for 2 years. Measurement will be scheduled for all patients at baseline and at follow-up, every 3 months for 2 years, including exacerbation rates, the modified British Medical Research Council dyspnea scale (mMRC), the COPD assessment test (CAT), the COPD clinical questionnaire (CCQ), physical variables, adverse events, medication administration, smoking status, and medical expenses. Pulmonary function tests will be conducted at the baseline and every 12 months thereafter. Figure 1 presents a flowchart of the trial procedures.

**Fig. 1 Fig1:**
[figure not shown]
Clinical trial design. COPD, chronic obstructive pulmonary disease; CAT, COPD assessment test; CCQ, COPD clinical questionnaire; mMRC, modified British Medical Research Council dyspnea scale

The primary endpoint includes the difference of FEV_1_ (including trough and peak) at 24 months from baseline and the number of acute exacerbations of COPD within 24 months between the two groups (mean values will be used in aggregation for the primary outcome data). Secondary endpoints include the following: trough and peak FEV_1_ at 12 months; the annual decline of FEV_1_, forced vital capacity (FVC), and FEV_1_/FVC (including trough and peak); duration, interval, and severity of COPD exacerbation; time to the first COPD exacerbation; quality of life (mMRC, CAT, and CCQ); medication administration and the use of rescue medications; and adverse events (Fig. 2).

**Fig. 2 Fig2:**
[figure not shown]
Summary of enrolment, interventions, assessments, and other activities at each study visit

### Recruitment and population

A total of 1000 subjects from 24 study sites in China with early-stage COPD (GOLD I and II) will be recruited. Half of the subjects will be screened from the rural communities, which are advertised for general population screening with a respiratory questionnaire and simple spirometry. The rest of them will be screened from the medical centers, which are outpatients with respiratory complaints. The majority of the subjects will be symptom-free or had very slight symptoms.

Subjects will be eligible for inclusion in this study only if all of the following criteria apply: (1) aged 40–80 years old, male or female, and community or outpatient; (2) has respiratory symptoms (chronic cough, sputum, or shortness of breath) and/or a history of exposure to risk factors (smoking, occupational exposure, indoor and outdoor air pollution, etc.); (3) clinical diagnosis of COPD (GOLD stages I and II): FEV_1_/FVC < 70% and FEV_1_ ≥ 50% predicted after 20 min with 400 μg of salbutamol inhalation (Ventolin, Glaxo Wellcome); (4) patients in a stable period, that is, near 4 weeks without COPD acute exacerbation; (5) the patients are able to communicate in words, agree, and have the ability to complete the test-related auxiliary examination; and (6) sign informed consent.

Subjects will be excluded for any of the following reasons: (1) suffering from major disease (except previously known COPD) such as severe heart, brain, liver, kidney, and blood system diseases, malignant tumors, and life-threatening pulmonary embolism, affect the study completed; (2) clinical diagnosis of lung cancer, pneumoconiosis, bronchiectasis, interstitial lung disease, bronchial asthma, active tuberculosisor, alpha1-antitrypsin deficiency, cystic fibrosis, or other simple restrictive ventilation dysfunction, affect the study outcome; (3) patients with contraindications such as allergic history, intolerance to the test drug, and suffering from severe gastric ulcer or small intestine malabsorption; (4) having chronic alcohol abuse, drug abuse, or any factors that affect compliance; (5) patients who have had undergone pneumonectomy; (6) subjects who are pediatric and pregnant or would be pregnant and breastfeeding; (7) suffering from COPD acute exacerbation within 4 weeks prior to the first visit, or hospitalization and/or antibiotic treatment and/or oral or intravenous therapy were required during the enrollment; (8) those who receive NAC for more than 3 months; (9) need long-term use of inhaled glucocorticoids, systemic (oral or intravenous) hormone dose instability (i.e., dose stabilization time is less than 6 weeks) or hormone dose exceeds the equivalent of prednisone 10 mg/day, or long-term use of antibiotics;(10) patients plan to receive long-term use of oxygen therapy or rehabilitation treatment in the next 2 years; and (11) the patient is currently participating in other clinical trials.

Trial center requirements: we do not have special requirements beyond the capacity of normal medical services, but the facilities should include spirometry instrument and chest X-ray/computed tomography (CT).

### Randomization and masking

The experiment was conducted by block randomization; the blind code was generated by a statistician from Rundo International Pharmaceuticals Research & Development Co, Ltd. using SAS V.9.2.2. After 1 week of the running-in period, eligible subjects were randomly assigned to the NAC group (one 600 mg tablet twice daily) or placebo (one tablet twice daily) for 2 years in a ratio of 1:1 by an independent statistician. In other research centers, participants were assigned to *N*-acetylcysteine or placebo according to their assigned numbers. The person analyzing the data will be blinded to the allocation.

NAC and placebo tablets are manufactured and packaged by Zhejiang Jinhua CONBA Bio-pharm. Co., Ltd. The placebo was packaged to be identical in composition, shape, color, and size to NAC tablets, but it did not contain any active ingredients. To prevent serious adverse events or other emergencies, each research center keeps a confidential envelope containing the information of uncovering blindness. If the envelope is used, it should be reported.

### Concomitant medication and treatment

In principle, long-term use of concomitant medication (define as continuous medication use for more than 1 month) should be avoided during the entire visit phase because the majority of enrolled subjects have extremely slight symptoms. However, individual therapy initiated before recruitment or clinical necessary treatment will be allowed. Medical intervention according to GOLD guidelines could be applied for less than 2 weeks if patients experienced a moderate or severe exacerbation.

### Measures

Regular visit with physical examination and symptom score documentation will be conducted after the first visit and then once every 3 months thereafter. Subjects will be asked details regarding whether they have health-related adverse events in the last 3 months, receive hospitalization or outpatient and treatment, experienced any acute exacerbation, and taken any medication (rescue drugs, antitussives, expectorants, inhaled corticosteroids/oral corticosteroids or antibiotics) at each visit. Adverse drug effects, self-reported smoking status, recent changes in current medication use, and any abnormal observations will be recorded in the case report form (CRF). We will issue a follow-up diary to the patient at each follow-up and check whether it is recorded on time at the next follow-up. All of the health visits, monitor method, and health education will be the same in both arms.

### Spirometry

Baseline and post-bronchodilator lung function will be assessed at follow-up visits at 12 and 24 months by measuring FEV_1_, FVC, FEV_1_/FVC, and FEV_1_% of the predicted value. In principle, each test will be conducted at the same time (± 2 h) in the morning. Spirometers should be standardized according to the American Thoracic Society (ATS) and European Respiratory Society (ERS) criteria [23]. For the same patient, each test will be performed by the same technician and the same equipment at each research center [23]. Spirometry will be performed before and after bronchodilation (salbutamol 400 μg will be inhaled 20 min prior to conducting reversibility testing). We request at least three acceptable efforts for each subject, up to eight forced expiratory manoeuvers. The optimal value of FEV_1_ and the optimal value of FVC in any of the three acceptable results (met the ATS/ERS criteria) will be used for data statistics and outcome analysis [23].

### Exacerbations of COPD

Patients have been requested to record their exacerbation information in the patient diary and collected at every follow-up. Acute exacerbation of COPD is considered to be due to exacerbation of respiratory symptoms (cough, expectoration, expectoration, wheezing, dyspnea, at least two new symptoms or aggravation of the original symptoms, and lasting for at least 48 h). Meanwhile, the following diseases should be ruled out: left or right ventricular dysfunction, pulmonary embolism, pneumothorax, pleural effusion, and arrhythmia [1, 24]. The duration of COPD exacerbation was defined as the date from the onset of acute exacerbation to the end of the event. The duration of hospitalization was defined as the time from admission to that of discharge from the hospital. The interval between the two times of COPD exacerbation was defined as the duration between the previous exacerbation event and the next event, and it should be noted that if the interval between two events was less than 7 days, they were regarded as the same event [1].

The severity of COPD exacerbation was categorized as mild, moderate, and severe as follows: mild, adding other common medications for COPD without outpatient hospital visit or hospitalization; moderate, exacerbation requiring outpatient or emergency room visit and the use of antibiotics and/or systemic glucocorticoids; or severe acute exacerbation requiring hospitalization [25]. Specifically, the date of each exacerbation and admission are being obtained, and the times to first exacerbation and admission will be calculated.

### Quality of life

Quality of life will be assessed at all outpatient visits using designated patient record questionnaires (CAT and CCQ) [26, 27]. The mMRC dyspnea score will be recorded at every visit.

### Recruitment strategy and quality control

As the incidence rate of chronic obstructive pulmonary disease is 13.7% in people over 40 years and over 70% of them are GOLD I–II in China, so we plan to screen 10,000 people in rural areas of Guangdong province within a year until half the target population is achieved. The other centers will screen subjects to achieve the rest of the population in urban areas (21 subjects/site).

Following applicable regulations and procedures, the monitor at each center is responsible for the inspection of compliance to the protocol in terms of study conduction and accurate and timely data items, for which the CRF will serve as the source document. The monitor will contact the site prior to the start of the study to review with the site staff the protocol, study requirements, and responsibilities of the staff to satisfy regulatory, ethical, and NAC requirements. We promise that the data of this trial is true, accurate, and complete, and the safety and rights of the subjects will be protected; the relevant researchers and the person in charge of the research center are authorized to use the spirometer, share the data, and consult all relevant documents. Good compliance is defined as the amount of drug used exceeds 80% of the predicted dose of the study drug.

### Informed consent

A trained research physician or investigator will introduce the trial to the patients and inform the patients of the details of the trial drug, including pharmacological components and adverse reactions. At the same time, informed consent in written form will be provided for patients to read. Only when patients fully understand the process of the trial, they can choose to participate voluntarily or give up. Subjects who are disabled in reading or writing should be informed through their guardians/caregivers and sign informed consent on behalf of them.

### Sample size and statistical methods

We determined the sample size with regard to the primary endpoint according to the PANTHEON study [9]. The sample size was calculated based on the difference between the peak and trough values of FEV_1_ in two groups: patients with mild-to-moderate COPD were included in this study. According to the early clinical trials, FEV_1_ of GOLD II COPD patients in the experimental group and the control group after 2 years were compared. The difference in valley value was 100 ml (standard deviation was 450 ml). Assuming that the test water is 5% and the test efficiency is 80%, each treatment group needs 318 patients to detect the difference in FEV_1_ trough between the two groups. Assuming a 35% drop-off rate, each group needs to be randomized at least 489 patients. Therefore, the overall sample size of this study needs 1000 patients.

Repeated measurement analysis of variance will be used to analyze the valley and peak value of FEV_1_, CCQ, and CAT data assessments. The annual decline rate of FEV_1_, FVC, and FEV_1_/FVC was analyzed by the random coefficient regression model. Assuming that the treatment effect changes linearly with the treatment time, the annual decline rate is represented by the regression coefficient of the model. The number and degree of acute exacerbation were compared by adjusted treatment exposure dose and over discrete Poisson regression. A log-rank test was used to compare the interval time of the first exacerbation of COPD. Fisher’s exact probability method was used to analyze the interval and duration of acute exacerbation of COPD, severity, and the use of rescue drugs. The frequency of rescue drugs will be further described. Before locking the database, the analysis plan will be explained in detail in a separately prepared statistical analysis plan (SAP).

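### The stated 80% power rests on an unlabelled SD and a GOLD II comparison after 2 years, and is not tied to the primary endpoint: 24-month FEV1 difference from baseline in GOLD I-II

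*Protocol article*

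**What the plan says.** The primary FEV1 endpoint, in Study design and again in Table 1, is the difference at 24 months from baseline, for trough and peak, between the two groups. Recruitment and population admits GOLD I and II, and "Half of the subjects will be screened from the rural communities".

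Sample size and statistical methods opens with: "The sample size was calculated based on the difference between the peak and trough values of FEV_1_ in two groups". It then says that "FEV_1_ of GOLD II COPD patients in the experimental group and the control group after 2 years were compared", and gives the inputs: "The difference in valley value was 100 ml (standard deviation was 450 ml". With a 5% test level and 80% power, "each treatment group needs 318 patients to detect the difference in" trough FEV1. Next comes the allowance for dropout: "Assuming a 35% drop-off rate, each group needs to be randomized at least 489 patients". The total is set at 1000.

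The same section names repeated-measures analysis of variance for trough and peak FEV1. It neither names nor excludes baseline FEV1 as a covariate, and it leaves detail to a separate SAP. Spirometry is scheduled at baseline, 12 months and 24 months.

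**The concern.** A power statement is useful only if its difference and SD refer to the quantity and population that will be analysed. Three things do not line up here.

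- **Quantity.** The sizing sentence reads as a comparison of FEV1 levels after 2 years; the endpoint is a change from baseline. The SD of a level and the SD of a change can differ widely, and 450 ml carries no label.
- **Description.** The opening sentence names the difference between peak and trough, which is not an endpoint of this trial. A few lines later the calculation is for trough alone.
- **Population.** The inputs come from GOLD II patients; the trial enrols GOLD I and II. No reason is given for carrying either figure across.

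At stake is whether a reader can tell what difference this trial can detect on its own primary endpoint. There is a related opportunity: baseline FEV1 is measured in everyone, and the way it enters the primary model affects precision.

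**Working it through.** **Inputs from the protocol:** difference 100 ml, SD 450 ml, test level 5% (sidedness not stated), power 80%, 1:1 allocation, dropout 35%, 1000 patients in total.

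**Assumed:** r, the correlation between baseline and 24-month FEV1, which the documents do not give; equal SDs at both times; large-sample normal formulas.

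**Step 1: reproduce the plan's figure.** n per arm = 2 × (1.96 + 0.8416)² × (450/100)² = 317.9, so 318, as stated. A one-sided test would give 251, so the plan used a two-sided 5% level. Dropout: 318/0.65 = 489.2, which matches the stated 489 apart from rounding. With 500 randomized per arm, 500 × 0.65 = 325 complete, and power for 100 ml with SD 450 ml is 80.9%.

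**Step 2: carry this to the stated endpoint.** If 450 ml is the SD of the level:

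- SD of the change = 450 × √(2(1 − r))
- residual SD after adjusting for baseline = 450 × √(1 − r²)
- detectable difference at 80% power = 2.80 × SD × √(2/325)

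For raw 24-month levels the detectable difference is 2.80 × 450 × √(2/325) = 99 ml. For the baseline-based analyses, with 325 per arm:

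| Assumed r | SD of change (ml) | Power for 100 ml, change | Detectable difference, change (ml) | Residual SD, adjusted (ml) | Power for 100 ml, adjusted | Detectable difference, adjusted (ml) |
|---|---|---|---|---|---|---|
| 0.3 | 532 | 67% | 117 | 429 | 84% | 94 |
| 0.5 | 450 | 81% | 99 | 390 | 91% | 86 |
| 0.7 | 349 | 95.5% | 77 | 321 | 98% | 71 |
| 0.8 | 285 | 99.4% | 63 | 270 | 99.7% | 59 |
| 0.9 | 201 | >99.9% | 44 | 196 | >99.9% | 43 |

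The change SD equals 450 ml only where 2(1 − r) = 1, that is, at r = 0.5. Only there does 318 per arm give the stated 80% for a change score. Below 0.5 the calculation is optimistic for change; above 0.5 it is conservative.

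**Step 3: gain from adjustment over the change score.** The variance ratio, adjusted to change, is (1 − r²)/(2(1 − r)) = (1 + r)/2. That is 0.65, 0.75, 0.85, 0.90 and 0.95 at r = 0.3, 0.5, 0.7, 0.8 and 0.9. In detectable difference the gain is 117 − 94 = 23, 99 − 86 = 13, 77 − 71 = 6, 63 − 59 = 4 and 44 − 43 = 1 ml.

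**Step 4: sensitivity to the population.** If the level SD in GOLD I-II were 500 or 600 ml (assumed values) instead of 450 ml, power for 100 ml on raw levels with 325 per arm would be 72% or 57%. This shows only that the GOLD II inputs matter; the documents do not give the GOLD I-II SD.

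**The case against.** The case on the other side is substantial, and much of it stands.

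- **No shortfall is shown.** For any r above 0.5, sizing on the level SD is conservative for a 100 ml effect on change. A reader might infer that the trial is underpowered; the documents do not support that. This stands.
- **The SD may already be that of the change.** The text does not label it. Reading it as the SD of the level is an inference from the sentence about comparing groups after 2 years. If it is the SD of the change, the mismatch of quantity disappears. This stands, and it is why the label is needed.
- **The endpoint already uses baseline.** A reader might set 99 ml for raw levels against 43 ml with adjustment and conclude that the plan discards most of its information. That is the wrong comparator: the endpoint is a difference from baseline, and a repeated-measures analysis with baseline as a time point also uses it. The fair comparison is change score against adjusted analysis, as in step 3.
- **Covariates belong in the SAP.** The article defers to an SAP that is not shown, so silence on a baseline covariate is not an error. This stands; naming it is a recommendation.
- **A smaller effect in GOLD I is conjecture.** The Introduction contrasts GOLD II with GOLD III, and for exacerbations. It says nothing on FEV1 in GOLD I, and the share of GOLD I patients is not given.
- **The peak/trough sentence is loose translation, and recruitment was due to end in August 2019.** Both are fair: the later sentence makes clear that trough was sized, and a rewrite is unlikely to change the sample size.

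None of this ties the 80% to the stated endpoint and population. Deferral to an SAP does not help, because the sample-size text itself uses one quantity and population and the endpoint definition another.

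**Conclusion.** The concern holds as a mismatch. The figure of 318 per arm is arithmetically right for a two-group trough comparison with a 100 ml difference and SD 450 ml from GOLD II patients. It is not shown to be right for the 24-month difference from baseline in GOLD I-II. If 450 ml is the SD of the level, power for a 100 ml change could lie anywhere from about 67% to over 99% across assumed r of 0.3 to 0.9, so the stated 80% tells the reader little about the actual endpoint. The direction of the error cannot be settled from the documents.

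Adjusting for baseline FEV1 is never less precise than the change score under the assumptions used. The gain is worthwhile at low r and modest at high r. The results rest on the assumed r, equal SDs at both times and 325 completers per arm.

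**What to change.** 1. In the sample-size section, state that 318 per arm is for a two-sided comparison of trough FEV1 with GOLD II inputs. Say whether 450 ml is the SD of the level or of the change. Give the reason for applying both inputs to GOLD I-II. Restate power or the detectable difference for the baseline-adjusted 24-month endpoint over a range of r, as in the table. Replace the wording about the difference between peak and trough.
2. In the primary repeated-measures FEV1 model, name baseline FEV1 as a covariate: the pre-bronchodilator value for trough and the post-bronchodilator value for peak, if that is how the full protocol defines them. Fix this in the SAP before the database is locked.

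GOLD stage and recruitment source as further covariates are optional and can be left to the SAP.

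Cost: text and model specification only. Baseline spirometry is already scheduled, so no patients, visits or measurements are added.

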We aimed to assess the beneficial effects of long-term treatment with high-dose NAC in patients with early-stage COPD regarding exacerbation rates and pulmonary function. The primary outcome measurement is FEV1 and the rate of acute COPD exacerbation. Discontinuations will increase with increasing study duration in long-term trials, and the rates are usually higher in the placebo group. The placebo group discontinuation rates in the ISOLDE, EUROSCOP, and UPLIFT studies ranged from 30 to 53%. In line with the UPLIFT protocol, we have estimated that the discontinuation rate is 35% in our study [41]. To ensure that it will be adequately powered to enable evaluation of the primary outcome, each group needs at least 500 random patients. Considering the need for acute exacerbations and lung function, the total required sample size of the study was 1000 patients. The majority of participants enrolled have no or extremely minor symptoms, and the mere presence of respiratory symptoms or gradually reduced lung function is an insufficient reason for patients to seek medical help [41]. In addition to the planned drug delivery and follow-up, we will provide health education, including counseling them to quit smoking, informing them of the benefits of early treatment, and providing other health advice. We will establish a good relationship with the research subjects and conduct regular telephone follow-up or Internet supervision to reduce the withdrawal rate.

In summary, because a dose-effect association has been demonstrated for NAC, this NAC-COPD trial will provide an opportunity to explore the effect of twice-daily NAC in patients with early-stage COPD disease. We postulated that an increased dose of NAC might lead to improved outcomes.

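### Repeated-measures ANOVA is named for the primary FEV1 outcome, but in its classical form it drops patients without a month-24 value and neither default test is the 24-month difference

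*Protocol article*

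**What the plan says.** All references are to the protocol article.

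- **Endpoint** (Study design; repeated in Table 1): the FEV1 part of the primary endpoint is "the difference of FEV_1_ (including trough and peak) at 24 months from baseline", compared between the two groups.
- **Schedule** (Study design): "Pulmonary function tests will be conducted at the baseline and every 12 months thereafter". There are thus three FEV1 values per patient, two of them after baseline.
- **Method** (Sample size and statistical methods): "Repeated measurement analysis of variance will be used to analyze the valley and peak value of" FEV1, and also for the CCQ and CAT scores. No term of the ANOVA is named as the primary test. The same section uses a random coefficient regression model for the annual decline rates, which are secondary.
- **Sample size** (same section): "The difference in valley value was 100 ml (standard deviation was 450 ml") and "Assuming that the test water is 5% and the test efficiency is 80"%. This gives 318 evaluable patients per group, raised to at least 489 for 35% loss and to 1000 in total.
- **Dropout** (Discussion): "Discontinuations will increase with increasing study duration in long-term trials, and the rates are usually higher in the placebo group". The section then adopts a single figure of 35% for this trial.
- **Deferral**: details are left to a separate SAP, which is not shown.

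**The concern.** The endpoint and the sample size refer to one quantity, the 24-month difference. The named method is built around others.

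1. **Incomplete patients.** Classical repeated-measures ANOVA needs every visit from every patient. Someone with baseline and month-12 spirometry but no month-24 test leaves the analysis altogether. With 35% loss planned for, this concerns a sizeable minority. Completers are protected by randomisation only if the reasons for leaving are unrelated to outcome or act alike in both arms, and the Discussion itself remarks that placebo groups usually lose more.
2. **Target.** The group main effect is a difference in the mean over visits. With three visits the group-by-time term has 2 degrees of freedom and asks whether the profiles differ in any way. Neither yields the month-24 estimate.

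At stake is whether the primary FEV1 result estimates the stated endpoint, and whether it does so free of selection among those who stayed.

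**Working it through.** **Step 1. Reproduce the plan's figure.** Inputs from Sample size and statistical methods: difference 100 ml, SD 450 ml, alpha 5% (taken as two-sided, which reproduces the stated number), power 80%.

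n per arm = 2 × [(1.960 + 0.842) × 450/100]² = 317.9, so 318, as stated. Allowing for dropout: 318/0.65 = 489.2, which agrees with 489 to within rounding. The plan's number is therefore a two-sample comparison at 24 months among the 65% who remain.

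**Step 2. Do the exclusions break the power?** 500 randomised per arm × 0.65 = 325 completers. SE = 450 × √(2/325) = 35.3 ml; 100/35.3 = 2.83; power = Φ(2.83 − 1.96) = 81%. They do not.

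**Step 3. What the default tests target.** Assume effects of 0, 50 and 100 ml at the three visits, SD 450 ml at each visit and an equal correlation ρ between visits. The effect pattern and ρ are assumptions.

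- Group effect over three visits: (0 + 50 + 100)/3 = 50 ml; SD of the mean = 450 × √[(1 + 2ρ)/3].
- Group effect over months 12 and 24: (50 + 100)/2 = 75 ml; SD = 450 × √[(1 + ρ)/2].
- Group-by-time, 2 df: noncentrality = (325/2) × [(0−50)² + (50−50)² + (100−50)²] / [450² × (1 − ρ)] = 812,500 / [202,500 × (1 − ρ)].

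| ρ | Group effect, 3 visits (50 ml) | Group effect, 2 visits (75 ml) | Group-by-time |
|---|---|---|---|
| 0.5 | 41% | 69% | 72% |
| 0.7 | 35% | 63% | 92% |
| 0.8 | 33% | 61% | 99% |
| 0.9 | 31% | 59% | >99% |

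The group effect would be badly powered under this pattern. The group-by-time test would mostly be well powered, but it gives no 24-month estimate.

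**Step 4. Bias from analysing completers.** Simulation with 1000 trials per setting, 500 per arm, a true 24-month effect of 100 ml and ρ = 0.8. Dropout after month 12 depends on the change seen at month 12, with a log-odds slope of 0.5, 1 or 2 per SD. The split by arm and the slopes are assumptions; the documents give neither. Monte Carlo error is about 0.7 ml.

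| Dropout, placebo/NAC | Completer estimate (slopes 0.5, 1, 2) | Estimate also using month-12 data |
|---|---|---|
| 35%/35% | 100.5, 99.6, 101.2 ml | 100.5, 99.8, 101.2 ml |
| 40%/30% | 94.7, 87.6, 83.9 ml | 101.4, 98.9, 100.3 ml |
| 45%/25% | 86.4, 77.9, 65.7 ml | 100.2, 100.5, 99.0 ml |

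With slope 0 (dropout unrelated to outcome) the completer estimate is 99.4 to 100.5 ml whatever the split. At 40%/30% the loss is about 5 to 16 ml. The larger losses in the last row need a 20-point gap between arms.

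**The case against.** The best defence has four parts.

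- **The power loss is conditional.** A reader might infer that the trial has 30 to 60% power rather than 80%. The documents do not support that: no ANOVA term is named as primary, and for an endpoint defined from baseline the group-by-time term is the natural one. The linear pattern is borrowed too. The sentence "Assuming that the treatment effect changes linearly with the treatment time" explains the random coefficient model for annual decline, not the ANOVA. If the effect were fully present by month 12, the post-baseline average would be close to 100 ml. This objection stands.
- **Unequal dropout is not a planning assumption.** A reader might take the Discussion to predict it for this trial. It makes a general remark and then applies one rate of 35% to both arms. This stands, so the size of the bias can only be shown as a range.
- **The bias is modest.** A loss of 5 to 16 ml compares with a standard error of about 35 ml on 24-month values, and in these settings it runs towards no effect. This is fair, but such bias does not shrink with sample size and can be reduced at almost no cost.
- **The SAP may settle it.** Covariance structure, missing-data rules and sensitivity analyses commonly belong there, and a mixed model may be meant by the label. Their absence from the article is therefore no finding. The article nevertheless names a method for a primary outcome, and as named it fits the endpoint poorly. It already uses a model that can keep incomplete patients for the secondary decline rates.

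**Conclusion.** The point holds in a limited form. As named, the method does not directly estimate the 24-month difference on which the endpoint and sample size rest, and in its classical form it discards month-12 data from patients without a month-24 value. That follows from the text and the definition of the method.

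The numerical consequences rest on assumptions. Completer bias is about 5 to 16 ml of 100 ml if dropout is 40%/30% and driven by first-year change, and nil if dropout is equal in this way or unrelated to outcome. Power of 31 to 41% (three visits) or 59 to 69% (two post-baseline visits) would arise only if the group main effect were the primary test and the effect grew linearly. The documents state neither. The planned power of about 81% for the 24-month comparison survives the exclusions, so this is no reason to call the trial underpowered. It is a reason to correct the named method before database lock.

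**What to change.** Replace repeated-measures ANOVA for FEV1, and likewise for CAT and CCQ, with a likelihood-based mixed model for repeated measures:

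- outcome: change from baseline, at each post-baseline visit;
- patients: all randomised with any post-baseline value, analysed as randomised;
- terms: treatment, visit, treatment-by-visit, baseline and baseline-by-visit, with unstructured covariance;
- primary FEV1 test and estimate: the treatment contrast at month 24.

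If the SAP already means such a model, it is enough to say so and to name the contrast. The model relies on dropout being explained by the observed values, and it recovers nothing for patients with no post-baseline spirometry. How far to probe that can be left to the SAP.

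The cost is a small change of wording and slightly more analysis work. The sample size of 1000 and the visit schedule do not change. The article describes follow-up as ongoing and places the SAP before database lock, so the change can be made before treatment codes are opened.
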